### 6.3 Contraindications

The methylprednisolone sodium succinate is contraindicated:

- in systemic fungal infections and patients with known hypersensitivity to the product and its constituents.
- for intrathecal administration. Reports of severe medical events have been associated with this route of administration.

### 6.4 Warning

#### Serious Neurologic Adverse Reactions with Epidural Administration

Serious neurologic events, some resulting in death, have been reported with epidural injection of corticosteroids. Specific events reported include, but are not limited to, spinal cord infarction, paraplegia, quadriplegia, cortical blindness, and stroke. These serious neurologic events have been reported with and without use of fluoroscopy.

The safety and effectiveness of epidural administration of corticosteroids have not been established, and corticosteroids are not approved for this use.

#### GENERAL

Increased dosage of rapidly acting corticosteroids is indicated in patients on corticosteroid therapy who are subjected to any unusual stress before, during, and after the stressful situation.

Results from one multicenter, randomized, placebo-controlled study with methylprednisolone hemisuccinate, an intravenous corticosteroid, showed an increase in early (at 2 weeks) and late

(at 6 months) mortality in patients with cranial trauma who were determined not to have other clear indications for corticosteroid treatment. High doses of systemic corticosteroids, should not be used for the treatment of traumatic brain injury.

**Cardio-renal**

Average and large doses of corticosteroids can cause elevation of blood pressure, salt and water retention, and increased excretion of potassium. These effects are less likely to occur with the synthetic derivatives except when used in large doses. Dietary salt restriction and potassium supplementation may be necessary. All corticosteroids increase calcium excretion. Literature reports suggest an apparent association between the use of corticosteroids and left ventricular free wall rupture after a recent myocardial infarction; therefore, therapy with corticosteroids should be used with great caution in these patients.

**Endocrine**

Hypothalamic-pituitary adrenal (HPA) axis suppression, Cushing's syndrome, and hyperglycemia. Monitor patients for these conditions with chronic use.

Corticosteroids can produce reversible HPA axis suppression with the potential for glucocorticosteroid insufficiency after withdrawal of treatment. Drug induced secondary adrenocortical insufficiency may be minimized by gradual reduction of dosage. This type of relative insufficiency may persist for months after discontinuation of therapy; therefore, in any situation of stress occurring during that period, hormone therapy should be reinstituted.

**Drug-Induced Liver Injury**

Rarely, high doses of cyclically pulsed intravenous methylprednisolone (usually for the treatment of exacerbations of multiple sclerosis at doses of 1 gram/day) can induce a toxic form of acute hepatitis. The time to onset of this form of steroid-induced liver injury can be several weeks or longer. Resolution has been observed after discontinuation of treatment. However, serious liver injury can occur, sometimes resulting in acute liver failure and death. Discontinue intravenous methylprednisolone if toxic hepatitis occurs. Since recurrence has occurred after re-challenge, avoid use of high dose intravenous methylprednisolone in patients with a history of toxic hepatitis caused by methylprednisolone.

## **Infections**

### ***General***

Patients who are on corticosteroids are more susceptible to infections than are healthy individuals. There may be decreased resistance and inability to localize infection when corticosteroids are used. Infections with any pathogen (viral, bacterial, fungal, protozoan, or helminthic) in any location of the body may be associated with the use of corticosteroids alone or in combination with other immunosuppressive agents. These infections may be mild, but can be severe and at times fatal. With increasing doses of corticosteroids, the rate of occurrence of infectious complications increases. Corticosteroids may also mask some signs of current infection. Do not use intraarticularly, intrabursally or for intratendinous administration for local effect in the presence of acute local infection. A study has failed to establish the efficacy of methylprednisolone sodium succinate in the treatment of sepsis syndrome and septic

shock. The study also suggests that treatment of these conditions with methylprednisolone sodium succinate may increase the risk of mortality in certain patients (i.e., patients with elevated serum creatinine levels or patients who develop secondary infections after methylprednisolone sodium succinate).

### ***Fungal infections***

Corticosteroids may exacerbate systemic fungal infections and therefore should not be used in the presence of such infections unless they are needed to control drug reactions. There have been cases reported in which concomitant use of amphotericin B and hydrocortisone was followed by cardiac enlargement and congestive heart failure (see CONTRAINDICATIONS and PRECAUTIONS, Drug Interactions, Amphotericin B injection and potassium-depleting agents). Special pathogens Latent disease may be activated or there may be an exacerbation of intercurrent infections due to pathogens, including those caused by Amoeba, Candida, Cryptococcus, Mycobacterium, Nocardia, Pneumocystis, Toxoplasma. It is recommended that latent amebiasis or active amebiasis be ruled out before initiating corticosteroid therapy in any patient who has spent time in the tropics or in any patient with unexplained diarrhea. Similarly, corticosteroids should be used with great care in patients with known or suspected Strongyloides (threadworm) infestation. In such patients, corticosteroid-induced immunosuppression may lead to Strongyloides hyperinfection and dissemination with widespread larval migration, often accompanied by severe enterocolitis and potentially fatal gram-negative septicemia. Corticosteroids should not be used in cerebral malaria. There is currently no evidence of benefit from

steroids in this condition.

### ***Tuberculosis***

The use of corticosteroids in active tuberculosis should be restricted to those cases of fulminating or disseminated tuberculosis in which the corticosteroid is used for the management of the disease in conjunction with appropriate antituberculous regimen.

If corticosteroids are indicated in patients with latent tuberculosis or tuberculin reactivity, close observation is necessary as reactivation of the disease may occur.

During prolonged corticosteroid therapy, these patients should receive chemoprophylaxis.

### ***Vaccination***

Administration of live or live, attenuated vaccines is contraindicated in patients receiving immunosuppressive doses of corticosteroids. Killed or inactivated vaccines may be administered. However, the response to such vaccines cannot be predicted.

Immunization procedures may be undertaken in patients receiving corticosteroids as replacement therapy, e.g., for Addison's disease.

### ***Viral infections***

Chicken pox and measles can have a more serious or even fatal course in pediatric and adult patients on corticosteroids. In pediatric and adult patients who have not had these diseases, particular care should be taken to avoid exposure. The contribution of the underlying disease and/or prior corticosteroid treatment to the risk is also not known. If exposed to chicken pox, prophylaxis with varicella zoster immune globulin (VZIG) may be indicated. If exposed to measles, prophylaxis with immunoglobulin

(IG) may be indicated. (See the respective package inserts for complete VZIG and IG prescribing information.) If chicken pox develops, treatment with antiviral agents should be considered.

### ***Neurologic***

Reports of severe medical events have been associated with the intrathecal route of administration (see ADVERSE REACTIONS, Gastrointestinal and Neurologic/Psychiatric).

### ***Ophthalmic***

Use of corticosteroids may produce posterior subcapsular cataracts, glaucoma with possible damage to the optic nerves, and may enhance the establishment of secondary ocular infections due to bacteria, fungi, or viruses. The use of oral corticosteroids is not recommended in the treatment of optineuritis and may lead to an increase in the risk of new episodes. Corticosteroids should be used cautiously in patients with ocular herpes simplex because of corneal perforation. Corticosteroids should not be used in active ocular herpes simplex.

## **PRECAUTIONS**

### ***General***

This product, like many other steroid formulations, is sensitive to heat. Therefore, it should not be autoclaved when it is desirable to sterilize the exterior of the vial. The lowest possible dose of corticosteroid should be used to control the condition under treatment. When reduction in dosage is possible, the reduction should be gradual.

Since complications of treatment with glucocorticoids are dependent on the size of the

dose and the duration of treatment, a risk/benefit decision must be made in each individual case as to dose and duration of treatment and as to whether daily or intermittent therapy should be used. Kaposi's sarcoma has been reported to occur in patients receiving corticosteroid therapy, most often for chronic conditions.

Discontinuation of corticosteroids may result in clinical improvement.

### ***Cardio-renal***

As sodium retention with resultant edema and potassium loss may occur in patients receiving corticosteroids, these agents should be used with caution in patients with congestive heart failure, hypertension, or renal insufficiency.

### **Endocrine**

Drug-induced secondary adrenocortical insufficiency may be minimized by gradual reduction of dosage. This type of relative insufficiency may persist for months after discontinuation of therapy; therefore, in any situation of stress occurring during that period, hormone therapy should be reinstituted. Metabolic clearance of corticosteroids is decreased in hypothyroid patients and increased in hyperthyroid patients. Changes in thyroid status of the patient may necessitate adjustment in dosage.

### **Gastrointestinal**

Steroids should be used with caution in active or latent peptic ulcers, diverticulitis, fresh intestinal anastomoses, and nonspecific ulcerative colitis, since they may increase the risk of a perforation. Signs of peritoneal irritation following gastrointestinal perforation in patients receiving corticosteroids may be minimal or absent. There is an enhanced effect due to decreased metabolism of corticosteroids in

patients with cirrhosis.

### **Musculoskeletal**

Corticosteroids decrease bone formation and increase bone resorption both through their effect on calcium regulation (i.e., decreasing absorption and increasing excretion) and inhibition of osteoblast function. This, together with a decrease in the protein matrix of the bone secondary to an increase in protein catabolism, and reduced sex hormone production, may lead to inhibition of bone growth in pediatric patients and the development of osteoporosis at any age. Special consideration should be given to patients at increased risk of osteoporosis (i.e., postmenopausal women) before initiating corticosteroid therapy. Local injection of a steroid into a previously infected site is not usually recommended.

### **Neurologic-Psychiatric**

Although controlled clinical trials have shown corticosteroids to be effective in speeding the resolution of acute exacerbations of multiple sclerosis, they do not show that corticosteroids affect the ultimate outcome or natural history of the disease. The studies do show that relatively high doses of corticosteroids are necessary to demonstrate a significant effect. An acute myopathy has been observed with the use of high doses of corticosteroids, most often occurring in patients with disorders of neuromuscular transmission (e.g., myasthenia gravis), or in patients receiving concomitant therapy with neuromuscular blocking drugs (e.g., pancuronium). This acute myopathy is generalized, may involve ocular and respiratory.

## **7. Organizational Structure**

## **7.1 Funding**

MARVEL trial is an investigator-initiated study which is organized by the second affiliated hospital of the Army Medical University and conducted in 82 centres in China. MARVEL will be funded by the National Natural Science Foundation of China. Methylprednisolone and its placebo are manufactured and provided by Chongqing Lummy Pharmaceutical Co., Ltd., Chongqing, China. The funder had no involvement in the study design, data collection, analysis and interpretation, writing or decision to submit the paper.

## **7.2 Trials Boards and Committees**

The following boards and institutions will assure the success of the clinical trial:

### **7.2.1 Steering Committee**

The Steering Committee of the clinical trial will decide on the final protocol and oversee the trial.

### **7.2.2 Data Safety and Monitoring Board**

The independent Data and Safety Monitoring Board (DSMB) will regularly monitor the safety of the trial and ensure the safety of patients at all stages of MARVEL. The independent DSMB will be composed of an experienced neurologist, a neuroradiologist, and a biostatistician, who are not participants of the MARVEL consortium and not involved in the clinical trial in any other way. The DSMB may at

any time propose to revise the clinical trial protocol or terminate the trial in case of safety concerns.

### **7.2.3 Ethics Advisory Board**

The Ethics Advisory Board (EAB) will supervise the trial and ensure that the trial is conducted in accordance with the ICH-GCP guidelines and international and China legislation. The EAB may at any time propose to revise the clinical trial protocol or terminate the trial in case of ethical concerns.

### **7.2.4 Imaging Core Laboratory**

Centralized imaging core laboratories will centrally blinded review all images and provide reference judgements for the definition of the per protocol population and intracranial haemorrhages. CT/MR and angiographic images will be independently reviewed by two independent central imaging core laboratories respectively. Imaging Core Laboratory will be independent to ensure it is blinded to the treatment allocation.

### **7.2.5 Clinical Events Committee**

The Clinical Events Committee will be comprised of three expert physicians independent of the investigational sites. This committee will validate all the complications that occur over the course of the study and categorize each for severity and relatedness according to the definition in the AE section. The Clinical Events Committee can request any additional source information and images supporting the AEs to assist with the adjudication.

## 8. Design

MARVEL is a multicenter, randomized, double-blind, placebo-controlled trial.

Patients will be randomized 1:1 to either Methylprednisolone Group or Placebo Group. The study has been registered at Chinese Clinical Trial Registry ([www.chictr.org.cn](http://www.chictr.org.cn), unique identifier ChiCTR2100051729).

## 9. Population

The patients for this trial will be recruited from AIS patients with large vessel occlusion within 24 hours from last known well.

### 9.1 Inclusion criteria

- Age  $\geq$  18 years;
- The time from onset to randomization was within 24 hours;
- Anterior circulation ischemic stroke was preliminarily determined according to clinical symptoms or imaging examination;
- Baseline National Institutes of Health Stroke Scale (NIHSS)  $\geq$  6
- Baseline Alberta Stroke Program Early CT Score (ASPECTS)  $\geq$  3;
- Computed tomography angiography (CTA) /magnetic resonance angiography (MRA) /digital subtraction angiography (DSA) confirmed occlusion of intracranial segment of internal carotid artery and middle cerebral artery, and decided to undergo endovascular therapy;

- Written informed consent signed by patients or their family members.

## 9.2 Exclusion Criteria

Patients meeting any of the following criteria will be excluded from study enrolment.

- Intracranial hemorrhage confirmed by cranial computed tomography (CT) or magnetic resonance imaging (MRI);
- mRS score  $\geq 2$  before onset;
- Pregnant or lactating women;
- Allergic to contrast agents;
- Allergic to glucocorticoids;
- Participating in other clinical trials;
- Systolic blood pressure  $> 185$  mmHg or diastolic pressure  $> 110$  mmHg, and oral antihypertensive drugs can not control;
- Genetic or acquired bleeding constitution, lack of anticoagulant factors; Or oral anticoagulants and INR  $> 1.7$ ;
- Blood sugar  $< 2.8$  mmol/L (50 mg/dl) or  $> 22.2$  mmol/L (400 mg/dl), platelet  $< 90 \times 10^9/L$ ;
- The artery is tortuous so that the thrombectomy device cannot reach the target vessel;
- Bleeding history (gastrointestinal and urinary tract bleeding) in recent 1 month;

- Chronic hemodialysis and severe renal insufficiency (glomerular filtration rate < 30 ml/min or serum creatinine > 220 umol/L [2.5 mg/ dL]);
- Life expectancy due to any advanced disease < 6 months;
- Follow-up is not expected to be completed;
- Intracranial aneurysm and arteriovenous malformation;
- Brain tumors with imaging mass effect;
- Severe systemic infectious diseases.

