#### **14.1.2 Randomization (R)**

If all inclusion criteria are met and no exclusion criteria are present, randomization will be performed.

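### Sections 6.3 and 9.2 disagree: a patient with a non-severe systemic fungal infection can satisfy the eligibility list although the protocol contraindicates the study drug

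*Supplement*

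**What the plan says.** All references are to protocol version 2.0.

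- **Section 6.3 (Contraindications)** says the drug is contraindicated "in systemic fungal infections and patients with known hypersensitivity to the product and its constituents". No degree of severity is attached to the infection.
- **Section 6.4 (Warning, Fungal infections)** repeats the point: "Corticosteroids may exacerbate systemic fungal infections and therefore should not be used in the presence of such infections". The one exception given there is use to control drug reactions, which is not the purpose of treatment in this trial.
- **Section 9.2 (Exclusion Criteria)** has one infection bullet, "Severe systemic infectious diseases", and two allergy bullets, "Allergic to glucocorticoids" and "Allergic to contrast agents". The synopsis carries the same three items.
- **Section 14.1.2 (Randomization)**: "If all inclusion criteria are met and no exclusion criteria are present, randomization will be performed".
- **Sections 13.4 and 13.4.1** call for the first dose as soon as possible after randomisation and recommend a start within 15 minutes.

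**The concern.** The exclusion list already carries some of the product's contraindications, since glucocorticoid allergy and serious systemic infection are both on it. It carries them in narrower words than section 6.3 uses. A site that works from the eligibility list and a site that works from the product section can reach opposite decisions about the same patient, and nothing in the protocol says which section governs.

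What is at stake is chiefly participant safety. The product text in section 6.4 warns that infections under corticosteroids can be severe and at times fatal, and that the drug may mask signs of infection. There is also a consistency cost. About 80 centres would each apply an undefined word during emergency enrolment, so who is enrolled at this margin depends on which section the site reads.

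**Working it through.** No sample-size or error-rate formula bears on this point, and the plan states no figure to reproduce. The check sets the contraindications beside the exclusions and then looks for any other step before the first dose that would catch the patient.

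**Step 1. Map section 6.3 onto section 9.2.**

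| Contraindicated in 6.3 | Matching exclusion in 9.2 and synopsis | Covered? |
|---|---|---|
| Systemic fungal infection, any severity | Systemic infectious disease, only if severe | In part: a case judged not severe is not excluded |
| Known hypersensitivity to the active drug | Allergy to glucocorticoids | Yes |
| Known hypersensitivity to another constituent of the product | None; the contrast-agent bullet concerns a different product | No, in principle |

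The protocol gives no definition of *severe* for the infection bullet. The severity grades in section 16.2.5 are for adverse events after enrolment. The constituents of the product are not listed, so the third row cannot be taken further from the documents.

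**Step 2. Look for a later check before dosing.**

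- Section 14.1.1 (Visit V0) asks the site to check the inclusion and exclusion criteria. It does not mention section 6.3.
- Section 14.1.2 makes randomisation follow from those lists.
- Section 17.1 lets the investigator withdraw a patient whose safety is endangered, and section 17.2 stops treatment when continuing would harm the patient or after anaphylaxis. Both act after enrolment, and the anaphylaxis rule acts only after exposure.

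No step between screening and first dose applies section 6.3.

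**Step 3. Ask whether the analysis rules would reveal such a patient.** Section 18.2.2 removes patients from the per-protocol population for, among other listed deviations, breaking an inclusion or exclusion criterion. A patient who passes 9.2 but is contraindicated under 6.3 has broken none. The listed criteria, which are stated as a minimum, would not flag the case on that ground.

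**Step 4. Size.** The documents give no frequency for systemic fungal infection or constituent allergy in this population. As a unit of scale, one such patient among the planned 1672 is 1/1672 = 0.06% of enrolment. Allocation is randomised 1:1, so these patients would fall in either group by chance, and their inclusion does not bias the comparison between groups.

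**The case against.** The strongest reply is that section 6 is not a trial rule. It is introduced as the manufacturer's summary of product characteristics, and it covers matters remote from this trial, such as epidural injection and vaccination. It also calls for a risk-benefit decision in the individual case. An investigator may well treat any systemic fungal infection as severe, in which case nobody slips through. The constituent-allergy limb cannot be demonstrated, because no constituents are listed. Sections 17.1, 17.2 and 19.1 add general safeguards.

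Much of this limits the point without removing it. The sponsor placed the contraindications in the protocol as the characteristics of the investigational product, and section 19.2 commits investigators to conduct the trial according to that protocol. Reading *severe* to include every systemic fungal infection is possible, but the text does not say so. The constituent limb should be held only as a gap in principle. The safeguards in 17.1 and 17.2 come too late to settle eligibility, though they do mean that such a patient need not complete the three-day course.

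A reader might go further and infer that 9.2 also admits patients with contraindicated tuberculosis or eye infection. Section 6.4 does say "The use of corticosteroids in active tuberculosis should be restricted to those cases of fulminating or disseminated tuberculosis" and "Corticosteroids should not be used in active ocular herpes simplex". These are warnings, however, and neither condition appears among the contraindications in 6.3. They can at most be considered in the same review. A reader might also want to attach a count of affected patients; the documents offer no basis for one.

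**Conclusion.** The conflict is real and current in version 2.0. For a patient with a systemic fungal infection judged not severe, section 9.2 permits randomisation and section 6.3 contraindicates the drug. For a known allergy to a non-glucocorticoid constituent the same mismatch exists in the wording, subject to what the constituents are.

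The conclusion rests on two readings: that *severe* restricts the infection bullet, and that section 6.3 is not meant to act as an unstated exclusion. Both follow from the text as written.

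The number of patients is unknown and probably small, because the infection or allergy must be known in someone presenting for endovascular treatment within 24 hours. On that assumption the effect on the primary estimate is negligible, and no effect on sample size or power can be shown. It would be wrong to infer that the trial's efficacy result is threatened, or that the documents settle which of the two sections should prevail. The point is one of participant safety and internal consistency, and it is worth correcting because the correction is cheap.

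**What to change.** Reconcile the infection bullet and the glucocorticoid-allergy bullet in section 9.2, the matching synopsis entries and the eligibility check at V0 with section 6.3, so that the protocol gives one answer for the same patient. Two mismatches need resolving: severe systemic infection against systemic fungal infection without a severity limit, and glucocorticoids against the product and its constituents. If *severe* is kept, define it for this criterion. If the constituents matter, name them or refer to where they are listed. The sponsor decides the clinical wording and which rule governs. The section 6.4 warnings on tuberculosis and ocular herpes may be looked at in the same pass, as a separate question.

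The cost is an amendment to two bullets, the synopsis and the checklist. The information can come from the medical history already taken at V0, with no new test. Depending on how the sponsor resolves it, a handful of patients may become ineligible.
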